**Figure 1 F1:**
[figure not shown]
**Health service perspective on non-adherence to CBT for anxiety disorders**.

We conclude that there is a need to examine carefully the external validity and effectiveness of CBT treatments for anxiety that have already been shown to be efficacious, and to identify factors that reduce non-adherence. In this study, we used these presumptions to plan for the examination of a new generation of CBT programs. With this understanding, we set out to define a protocol for examination of the effectiveness of cell phone-supported CBT for anxiety disorders in frontline settings that also allows to evaluate adherence to therapy. Specifically, the aims of this study were to define a protocol for assessment of

• the superiority of cell phone-supported CBT (CBT-cell phone) treatment against anxiety disorders compared with CBT treatment as usual (CBT-TAU), and

• adherence with CBT-cell phone compared with CBT-TAU and CBT provided with access to a placebo technical device (CBT-placebo).

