#### Study outcome measures

The primary outcome measure is the Beck Anxiety Inventory [BAI]. The BAI [25] is a 21-item symptom checklist rated on a 4-point scale (0-3). The main secondary set of outcome measures describes patient adherence. Data on adherence are collected in 4 dimensions from the therapists after the last session; that is whether the client has

• discontinued the CBT program by not showing up at sessions;

• discontinued the CBT program by actively informing the therapist;

• been discontinued from the treatment by the therapist; and

• not fulfilled the therapeutic contract, e.g. by not completing homework agreed upon.

The remaining secondary outcome measures are HADS-A and -D, and the General Health Questionnaire [GHQ-12]. The outcome measures are administered on each of 3 occasions: pre-treatment, when the participants had completed their programme, and with follow-up at 6 months. The GHQ has demonstrated validity with young adults (17+ years) from the United Kingdom [26]. The sensitivity and specificity for both HADS-A and HADS-D are similar to the sensitivity and specificity achieved by the GHQ and they perform well in assessing the symptom severity of anxiety disorders and depression in both somatic, psychiatric and primary care patients, and in the general population [27].

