### Statistical analysis

Power calculations were performed to determine the minimum sample size needed to fulfil the research aims. The calculations were based on change scores (pre- to post-treatment) between groups in 2 previous studies comparing CBT as usual with CBT supported by handheld computers [28] and CBT provided by stationary surgery-located computers [9]. To detect a standard deviation difference of 0.3 in BAI change scores at 80% power and with 0.05 alpha, we determined that a total sample size close to 150 per stand (450 in total) was needed.

For each of the outcome measures, a series of mixed effects models will be considered. Such models are described in detail by Everitt and Pickles [29]. Model adjustments will be used to analyse associations between pre- and post-randomization values of outcome (i.e. post-CBT and 6 months follow-up), treatment, drugs, and parallel depression. For dimensional outcomes (anxiety scores), ITT analyses will be conducted using all participants enrolled in the study, and the last available data point will be used as the post-treatment score. Uncontrolled effect sizes will be calculated for pre- to post-treatment change. For categorical outcomes (adherence), treatments will be compared using Pearson's chi-square test, Fisher's exact test, or logistic regression, as appropriate.

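### The last-value rule scores a client with no later BAI as zero change, which biases the primary contrast if missing BAI differs by arm and those clients truly changed

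*Protocol article*

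**What the plan says.** All references are to the protocol article.

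- **Missing-data rule (Statistical analysis).** The analysis of dimensional outcomes, identified as those measuring anxiety, takes in everyone enrolled under intention to treat. Where a value is missing, the rule is that "the last available data point will be used as the post-treatment score". This covers the BAI, which Study outcome measures names as primary.
- **Model (same paragraph).** "For each of the outcome measures, a series of mixed effects models will be considered". Nothing says how these models and the last-value rule fit together.
- **Schedule (Study outcome measures).** "The outcome measures are administered on each of 3 occasions: pre-treatment, when the participants had completed their programme, and with follow-up at 6 months".
- **Adherence.** The second aim, at the end of Background, is to assess "adherence with CBT-cell phone compared with CBT-TAU and CBT provided with access to a placebo technical device". Study outcome measures adds: "The main secondary set of outcome measures describes patient adherence". Three of its four dimensions are forms of discontinuation; the fourth is an unfulfilled therapeutic contract, such as homework not done.
- **Dropout.** The Study protocol section calls dropout in earlier computer-supported studies substantial. No rate is given for this trial.

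**The concern.** Only the baseline BAI precedes the post-treatment score, and the post-treatment assessment is tied to finishing the programme. For a client who leaves early and gives no later BAI, the last available point is the baseline, and the analysis treats a change of zero as if it had been measured. Read literally, the rule could also let a 6-month value stand in as the post-treatment score for a client who missed only the middle assessment. The article does not settle this.

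Background cites large pre-to-post improvements with CBT, so zero is not obviously a neutral value. If one arm returns more post-treatment questionnaires than another, part of the BAI difference may reflect questionnaire return rather than anxiety. If missingness is equal, a real effect can be diluted. A trial that compares adherence across arms is exposed to both.

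**Working it through.** **Inputs from the article:** design difference 0.3 SD in BAI change, 80% power, alpha 0.05, about 150 per arm (Statistical analysis).

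**Assumed, because the article gives no figures:** *m*, completers' mean improvement, 0.8 SD (range 0.5 to 1.5); *c*, the true mean improvement of clients with missing post-treatment BAI; *d*, the share missing. The SD of change is set to 1.

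**1. The plan's own figure.** n per arm = 2(z_alpha + z_power)²/0.3².
- Two-sided: 2 × 7.849/0.09 = 174.4, so 175.
- One-sided: 2 × 6.183/0.09 = 137.4, so 138.

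Neither gives 150. That is a separate matter, but it sets the comparator: at 150 per arm, two-sided power with no missing data is 73.8%, not 80%.

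**2. Bias under the rule (no BAI after baseline).** The true arm mean is (1 − d)m + dc. The rule reports (1 − d)m. Each arm's improvement is therefore understated by dc, and the bias in the contrast is c × (d_TAU − d_cell). With 30% missing in TAU and 15% in the cell phone arm:
- c = 0.8: 0.8 × 0.15 = 0.12 SD, which is 40% of the 0.3 SD target
- c = 0.4: 0.4 × 0.15 = 0.06 SD
- c = 0: nil

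**3. Type I error when c = m, so that the arms truly do not differ.** The variance of the scored change in one arm is (1 − d) + d(1 − d)m². With m = 0.8:
- d = 0.30: 0.70 + 0.21 × 0.64 = 0.8344
- d = 0.15: 0.85 + 0.1275 × 0.64 = 0.9316
- SE = √((0.8344 + 0.9316)/150) = 0.1085, and 0.12/0.1085 = 1.106
- Two-sided rejection rate at 1.96: 19.8%

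At 30% vs 20% missing, the false difference is 0.08 SD and the rejection rate 11.5%. Over m = 0.5 to 1.5, the same 10-point gap gives 0.05 to 0.15 SD and 8% to 23%.

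**4. Equal missingness, true effect 0.3 SD, same benefit in clients with missing BAI.** The effect becomes 0.3 × (1 − d). Two-sided power at 150 per arm with m = 0.8:

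| Missing | Effect under the rule | Power under the rule | Power, observed cases only |
|---|---|---|---|
| 0% | 0.30 SD | 73.8% | 73.8% |
| 20% | 0.24 SD | 56.9% | 64.2% (120 per arm) |
| 30% | 0.21 SD | 48.5% | 58.5% (105 per arm) |

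The rule itself costs 64.2 − 56.9 = 7.3 points, or 58.5 − 48.5 = 10.0 points. The rest of the fall from 73.8% is lost information. The cost depends on m: power under the rule at 20% and 30% missing is 60.5% and 53.3% for m = 0.5, and 46.3% and 36.3% for m = 1.5.

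**The case against.** The strongest defence is that zero may be right. If clients who abandon therapy do not change, carrying the baseline forward is correct on average, and a difference between arms is a real consequence of better retention, in line with the intention-to-treat principle under Procedures. This stands as a condition: the bias exists only if those clients' true mean change is not zero.

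Four stronger readings are tempting, but the article does not support them.

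- **That any adherence difference becomes a false anxiety effect.** Adherence is not the same as missing BAI. Undone homework need not leave the BAI missing, and a client who stops sessions may still fill it in. Under Ethical considerations, clients may leave the study and still receive routine CBT. Limitations claims complete follow-up data; no procedure for obtaining BAI from clients who leave is described, so that claim does not remove the risk.
- **That the second aim predicts an adherence difference.** It only compares adherence; superiority is claimed for anxiety alone.
- **That the rule contradicts the mixed models.** The article leaves the two unreconciled, which is less than a contradiction.
- **That the whole fall in power is due to the rule.** Most of it comes from the starting power of 73.8% and from the missing outcomes, which no analysis fully recovers.

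A mixed model is not assumption-free either. It relies on missing at random, and if baseline BAI is only a covariate, a client with baseline alone contributes nothing. Both points stand and shape the fix.

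**Conclusion.** The concern holds as a conditional bias in a rule that the article itself fixes for the primary outcome. It arises if the share with missing post-treatment BAI differs by arm and those clients' true mean change is not zero; its size is the product of the two. For a 15-point gap, the false difference runs from nil to 0.12 SD as the true change runs from zero to 0.8 SD, and the type I error of about 20% belongs to the upper end only. With equal missingness of 20% to 30%, the rule itself costs about 7 to 10 points of power, assuming m = 0.8 and the same benefit in clients with missing BAI.

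All missingness rates and changes are assumptions, so these figures show what the rule can do, not what will happen in this trial. The zero-change result applies to clients with no BAI after baseline; whether a 6-month value may replace a missing post-treatment one is a second, unresolved ambiguity.

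**What to change.** - Delete the last-value rule as the primary approach.
- Make the primary analysis a likelihood-based mixed model on observed BAI, with baseline, post-treatment and 6 months all as outcomes and baseline means constrained equal across arms. Every randomised client with a baseline value then stays in the model, and a 6-month value is analysed at its own time point.
- Name the cell phone vs TAU contrast at post-treatment as the primary test.
- State the missing-at-random assumption explicitly.
- Keep two sensitivity analyses: carry-forward of the baseline, and one assuming worse outcomes after dropout.

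The cost is a change of wording, slightly more analysis work, and reliance on a stated missing-at-random assumption. No new data are needed, and the model class is one the article already names.

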#### Procedures

The procedure follows the intention to treat (ITT) principle, that is, based on the initial treatment intent, not on the treatment eventually administered. The Unga Vuxna service accepts clients following a therapist telephone triage. Recruitment to the study is administered in association with the first CBT session at the clinic. At this session, routine screening is performed by administrating the Hospital Anxiety and Depression Scale (HADS) to clients. Individuals found fitting the study criteria are presented with information materials about the study by a study nurse. The materials are made available to the client for evaluation in private without the therapist being present. The allocation schedule is generated by a biostatistician outside the clinic before the study commences using an individual unit of randomization. Individuals who fit the inclusion criteria and have consented to participate are stratified according to whether they are prescribed medication or not (yes, no) and with regard to their HADS-D score. They are then randomly allocated to receive CBT-cell phone, CBT-TAU, or CBT-placebo (Figure 4). To parallel the IT-lending situation in the CBT-cell phone strand (in adherence analyses), the clients allocated to CBT-placebo are provided with an MP3-player with anti-stress materials to use between the sessions. The sealed envelopes are opened in strict numerical sequence by the study nurse. The nurse is instructed to spend no more than 10 minutes before and after each session with each client.

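### Adherence may be tested by methods that ignore the randomisation strata; if those strata predict adherence, such a test is conservative and loses a little power (minor, fixed in one sentence)

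*Protocol article*

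**What the plan says.** Under Procedures, consenting clients are "stratified according to whether they are prescribed medication or not (yes, no) and with regard to their HADS-D score" and then "randomly allocated to receive CBT-cell phone, CBT-TAU, or CBT-placebo". The HADS-D cut-point, the number of levels and any block scheme are not given.

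The aims at the end of the Background make adherence the second aim and compare the cell-phone arm with both TAU and placebo. Study outcome measures gives its rank: "The main secondary set of outcome measures describes patient adherence". Therapists report it in four dimensions, once, after the last session.

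Statistical analysis contains two sentences that bear on how adherence is analysed. The general one reads "For each of the outcome measures, a series of mixed effects models will be considered" and is followed by a list of adjustments ("i.e. post-CBT and 6 months follow-up), treatment, drugs, and parallel depression"). The specific one reads "For categorical outcomes (adherence), treatments will be compared using Pearson's chi-square test, Fisher's exact test, or logistic regression, as appropriate". It names no covariates and gives no rule for choosing among the three methods.

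**The concern.** When a factor is used to restrict randomisation and also predicts the outcome, the analysis should include it. A pooled two-by-two test counts the between-stratum variation in adherence as noise. If the design has already removed that variation from the arm comparison, the test's variance is too large: it rejects too seldom when there is no effect and detects a real effect less often. Low mood and existing medication could plausibly bear on dropout, though the documents give no figures for this.

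At stake is some sensitivity on the second aim's two contrasts. Two of the three methods named for adherence cannot take the strata into account, and the article does not say that the third will.

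**Working it through.** **The plan's own figures.** The plan gives no error rate, power or expected rate for adherence, so there is no adherence figure to reproduce. Its 150 per arm belongs to the BAI comparison. For 0.3 SD at 80% power, 2(1.960 + 0.842)²/0.3² gives 175 per arm two-sided, and 138 with a one-sided 0.05. Neither equals 150, but that is a separate matter. Here 150 per arm is simply taken as given.

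**Inputs from the article.** Three arms of about 150 (450 in total); strata from medication (yes/no) and HADS-D; alpha 0.05.

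**Assumptions.** HADS-D in two levels, giving four equal strata; allocation balanced within strata; overall non-adherence 30% to 34%; each factor acting on non-adherence with the same odds ratio (OR); two arms compared; treatment OR 0.5 for power.

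**Formula.** With stratum shares w, stratum risks p and overall risk p̄, the ratio of the actual variance to the variance Pearson's test uses is

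r = Σ w p(1−p) / [p̄(1−p̄)],

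and the true two-sided level is 2[1 − Φ(1.96/√r)].

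*Worked case, OR 2 for each factor.* The risks are 0.180, 0.305, 0.305 and 0.468, with mean 0.314. The mean of p(1−p) is (0.148 + 0.212 + 0.212 + 0.249)/4 = 0.205. The denominator is 0.314 × 0.686 = 0.215. So r ≈ 0.952 and the level is about 4.5%. Simulation gives 4.6%.

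**Simulation** (100,000 runs per cell; Pearson against Cochran-Mantel-Haenszel, CMH):

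| OR per factor | r | Level: Pearson / CMH | Power: Pearson / CMH | Points lost |
|---|---|---|---|---|
| 1 | 1.000 | 5.0% / 5.0% | 71.0% / 71.0% | 0.0 |
| 1.5 | 0.982 | 4.7% / 4.9% | 73.6% / 74.1% | 0.5 |
| 2 | 0.952 | 4.6% / 5.0% | 69.8% / 71.2% | 1.4 |
| 3 | 0.890 | 3.8% / 4.9% | 65.1% / 68.8% | 3.7 |
| 5 | 0.790 | 2.7% / 4.9% | 58.6% / 67.0% | 8.4 |

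The overall risk differs slightly between rows, so compare within a row. The OR 5 row is a stress case.

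**Unequal strata.** A second set assumes 40% medicated, 40% with high HADS-D, and a treatment log-odds ratio of −0.75 (8,000 null and 5,000 alternative runs). ORs are given as HADS-D / medication:

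| ORs | Pearson level | Power: Pearson / CMH | Points lost |
|---|---|---|---|
| 2 / 1.5 | 4.7% | 72.9% / 73.6% | 0.7 |
| 3 / 2 | 3.8% | 71.3% / 73.2% | 1.9 |
| 4 / 3 | 3.7% | 67.2% / 71.6% | 4.4 |

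The stratified test's level stayed between 4.9% and 5.5%. A repeat under the same ORs gave Pearson levels of 4.7%, 3.9% and 3.7%, and losses of about 0.8, 2.1 and 4.7 points. Fisher's exact test would be more conservative than Pearson's.

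**Dependence on blocking.** Without blocking within strata, Pearson's test keeps its nominal 5% level. A similar power gain from using the strata remains.

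**The case against.** **The plan does not commit to an unstratified test.** This is correct. Logistic regression is in the same sentence, and a reader who infers that Pearson or Fisher will be used goes beyond the text. What stands is that an analyst who used a plain chi-square test would be following the protocol as written.

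**The section already adjusts every outcome for drugs and depression.** The general sentence does speak of each outcome measure, and the adjustments match the stratification factors. But the adjustment is worded for values of an outcome before and after randomisation. Adherence has no pre-randomisation value and is recorded once. It then receives its own test sentence without covariates, and Pearson's and Fisher's tests cannot carry any. The adjustment may have been meant to reach adherence, but the text does not clearly say so.

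**Covariate lists and the choice among tests belong in a statistical analysis plan.** This is largely fair. The missing rule for choosing is not itself the point here, and neither is any inference that a p-value would be selected. The point is narrower: the article does name the permitted tests, and two of them ignore its own design.

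**An off-nominal error rate suggests false positives.** The documents do not support that reading. With balanced strata the level can only fall below 5%.

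**The loss is assumed, and small.** This also stands. At ORs 2/1.5 the simulated level of 4.7% lies within about 1.2 Monte Carlo standard errors of 5% (√(0.05 × 0.95/8000) = 0.24 points), and the power loss is under 1 point.

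**Conclusion.** The point holds as a minor one. Randomisation is stratified, and the adherence sentence permits two tests that ignore the strata beside a logistic regression with no stratum terms stated.

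The cost arises only if such a test is used and the strata predict adherence. Under the assumptions above, the loss is 0 to 1.4 power points for stratum odds ratios up to 2 and roughly 2 to 5 points at 3 to 4. It is nil if the strata are not prognostic. The drop below the nominal 5% also requires allocation balanced within strata, which the article does not state.

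It would be wrong to conclude that aim 2 has an invalid test or that a power loss is certain. The documents support neither. The primary BAI analysis is not affected.

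**What to change.** In Statistical analysis, replace the three-way choice for adherence with one analysis: logistic regression on arm plus baseline medication (yes/no) and baseline HADS-D, using the values that governed randomisation. Report the two contrasts of the second aim, CBT-cell phone against CBT-TAU and CBT-cell phone against CBT-placebo. If counts are too sparse for the model, use a Cochran-Mantel-Haenszel or stratified exact test over the randomisation strata in place of the unstratified Pearson or Fisher test.

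The cost is one sentence of wording. Both factors are already recorded for randomisation, so no new data or participants are needed. In the simulations, the stratified test was never materially worse than the pooled one, even when the strata had no effect.

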### Ethical considerations

The study protocol was approved by the Regional Research Ethics Committee in Linköping in 2009 (Dnr. 111-09). Before submission to the committee the protocol was reviewed with regard to ethical issues related to the participants, particularly considering non-malfeasance, autonomy, and fidelity [30]. Prior to invitation and randomization, clients displaying signs of severe psychiatric disease are referred to psychiatric specialists. The research will contribute to the development of the evidence base in the area, with potential future benefits for participants and society. All participation will be based on informed consent. The clients will be able to withdraw from the study at any time, while still being supplied routine CBT services. The integrity of the randomization procedure will be checked on a regular basis.

## Discussion

Health care services are increasingly moving out of the physician's office into IT-mediated treatment in the community [18,31]. There is evidence that IT-supported therapy works in controlled settings [20]. However, if evidence is to be translated from stringent RCTs to frontline clinical practice, some obstacles still remain before IT-supported therapy can become routine practice. Two particular differences between evidence from RCTs and frontline clinical settings that need to be investigated are their applicability to total populations and on clients with overt comorbidity. In addition, there are a host of organizational and community context issues that can only be investigated in real-world settings.

Different applications of cell phone support for in situ CBT have recently been reported [32]. The present protocol can be used to study the effectiveness of cell phone-supported CBT for management of anxiety in different practice, organizational, and technical settings. We recognize the lessons learned from early innovative studies that had methodological shortcomings preventing them from transforming from evidence to practice [21]. Although different types of software applications for diagnosis and treatment of anxiety syndromes are available off-the-shelf for stationary computers and the Internet, the availability of high-quality applications for portable computers and cell phones is scarce. To allow the CBT-cell-phone strand to be replicated in other studies, the design of the application used in the case study setting will be described in detail in forthcoming reports.

### Limitations

The study protocol complies with allocation concealment and completeness of follow-up data. However, because of the tangible nature of cell-phone supported therapy, blinding is not supported by the protocol. After having been allocated a client and a treatment in a concealed process, the therapist has total insight in the therapy and, thereby, any use of supportive technologies is not blinded.

